### Control intervention

3.3

The control group will receive an educational 6-session intervention, daily administered, on the following topics: a) healthy lifestyle (diet and nutrition); b) stress management; c) regulation of circadian rhythms; d) management of medication side effects (**Table 4**). The control group intervention will be administered with interacting sessions lasting 60–90 minutes provided within the group context. At the end of each session, participants will receive informative leaflets and cards summarizing the key-points addressed during the session. A dedicated training material will be provided to all staff members in order to guarantee the fidelity of administration of all sessions of the control intervention.

**Table 4 T4:** Characteristics of each module of the control intervention.

Module	Description
Healthy lifestyle (diet and nutrition) [figure not shown]	The module emphasises the importance of a varied and balanced diet for maintaining energy levels, a healthy weight and general well-being. It includes practical advice on calorie distribution throughout the day, regular consumption of fruit and vegetables, choosing whole grains and staying hydrated.
Healthy lifestyle (physical activity) [figure not shown]	The module promotes daily exercise as a means of improving sleep, mood, weight and quality of life. Simple ways to increase the amount of time spent being active and reduce sedentary behaviour are suggested.
Stress management [figure not shown]	The module helps to recognise physical, emotional and cognitive manifestations of stress and suggests immediate management exercises (breathing, muscle relaxation, music). The aim is to reduce the impact of stress in everyday life and prevent relapses.
Regulation of circadian rhythms [figure not shown]	The module explores the role of sleep in maintaining mental and physical health, linking insomnia and irregular sleep to irritability, reduced concentration and physical problems. It provides environmental, dietary and behavioural guidelines to promote a healthy sleep-wake cycle.
Management of medication side effects [figure not shown]	The module clarifies that mental disorders benefit most from a combination of pharmacological treatment and psychotherapy. It reduces prejudices about drugs, explains the main categories used and emphasises the importance of therapeutic adherence to prevent relapses.

All images were generated using AI.

## Training of mental health professionals

4

All mental health professionals involved in the study protocol will be adequately trained in an *ad hoc* 4-day training course about the use of the experimental and control interventions. During the training, learning material explaining how to conduct the experimental and control interventions will be provided to all mental health professionals. In addition, specific learning role-play sessions will be organized to test both interventions in all trainers, under the supervision of a specialized and experienced trained clinician. All mental health professionals who will be involved in the assessment phase of the study protocol will be adequately trained and instructed about all assessment tools and instruments, before the start of the intervention.

## Statistical analysis

5

Sample size has been calculated using the Statistical Software G*Power version 3.1. (Franz, Universitat Kiel, Germany). Based on the primary objective of the study, in order to detect any difference in the mean scores of the subscales of the DERS between the control and the experimental groups, by keeping a statistical power of 0.95 to identify an effect size of 0.8 (α=0.05, two-tailed) and taking into consideration all variables to be entered in the t-test. A total sample size of 84 was established to be reached for the present study (42 participants for each group). Considering the longitudinal follow-up and the clinical instability of the study population, attrition and missing data are expected. Analyses will be conducted on available data, with attrition rates systematically reported. Given the pilot nature of the trial, results will be interpreted with a focus on feasibility and preliminary efficacy. The IBM Statistical Package for Social Sciences software, version 26 (SPSS, Chicago, Illinois, USA), will be used for the data analysis. Descriptive analyses will be performed to describe the socio-demographic characteristics of the sample and to assess the normality of the data. Categorical variables will be summarized as frequency (n) and percentage (%), while continuous variables will be summarized as mean and standard deviation (SD). Categorical variables will also be compared using the χ^2^-test and *post-hoc* tests. To summarize the data and test the differences based on categorical analysis, parametric tests (t-test or ANOVA) or non-parametric tests (Kruskal-Wallis test or Mann-Whitney U test) will be used, depending on the normality of the data. To compare longitudinal data, the paired t-test or Wilcoxon test will be used, again based on normality. Finally, correlation and regression analyses (univariate/multivariate, linear/logistic) will be conducted, including socio-demographic and clinical variables and the total scores and subscales of the various scales, to explore any relationships between the different factors. The statistical significance cut-off will be set at p <0.05.

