This study has some potential limitations. First, it is a pilot trial with a relatively small sample recruited from a single centre, factors that could potentially limit the generalisability of the results. However, if the results confirm the expected efficacy, the protocol may serve as a model that can be replicated in other hospital and community settings, helping in increasing evidence at its support, with significant implications for the secondary and tertiary prevention of adolescent psychiatric disorders. At the same time, the diagnostic heterogeneity of participants could lead to an increased variability in outcomes and make it difficult to interpret results. However, this reflects the clinical reality of patients admitted to our ward in this age group, which cannot be excluded. Accordingly, the primary aims of this study are to evaluate feasibility and preliminary efficacy, rather than disorder-specific treatment effects. Furthermore, the target population, consisting of adolescents and young adults in the acute phase, may experience levels of emotional instability that could affect their consistent participation in sessions and completion of follow-up assessments. At the same time, systematic feedback from participants, collected through satisfaction questionnaires, will allow the programme to be further refined to better meet the needs of young users, improving the intervention and promoting patients engagement. A further limitation concerns the possible confounding effect of concomitant pharmacological and psychotherapeutic treatments, which are difficult to control in a real clinical setting. Although we recognize that in a natural clinical setting, complete control of concomitant treatments cannot be guaranteed, measures will be taken (detailed recording of treatment regimens, statistical control, and subgroup analysis) to minimize variability caused by treatment changes and to strengthen the reliability of causal inferences in this protocol.

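### The stated power of 0.95 is the figure with no losses, yet the same paragraph expects attrition and analyses available data only

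*Protocol article*

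**What the plan says.** All the elements stand in one paragraph, section 5 (Statistical analysis) of the protocol article.

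- **Target:** "by keeping a statistical power of 0.95 to identify an effect size of 0.8 (α=0.05, two-tailed".
- **Comparison:** the aim is to "detect any difference in the mean scores of the subscales of the DERS between the control and the experimental groups", using a t-test.
- **Resulting number:** "A total sample size of 84 was established to be reached for the present study (42 participants for each group".
- **Losses:** because of the longitudinal follow-up and "the clinical instability of the study population, attrition and missing data are expected". The paragraph then says that available data will be analysed and attrition rates reported.
- **Interpretation:** as a pilot, the trial is to be read for feasibility and preliminary efficacy.

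The limitations part of section 6 (Discussion) repeats the expectation of loss. It says that these patients may have "emotional instability that could affect their consistent participation in sessions and completion of follow-up assessments".

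The paragraph gives no attrition rate, no inflation of the sample size and no power for a reduced number of patients. It does not name the assessment (T1 to T5) to which the calculation applies.

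**The concern.** A power figure belongs to the number of patients who enter the test, not to the number randomised. If 84 is just enough for 0.95 with complete data, and the plan itself expects incomplete data with no stated allowance, then the plan quotes a power that its own design is not expected to deliver.

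The type II error is at stake. A reader takes it to be 5% for an effect of 0.8. With losses it is larger, by an amount that the document does not let the reader work out. The question is whether 84 contains a hidden margin and, if not, how fast power falls.

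**Working it through.** **Inputs from section 5:** d = 0.8, two-sided alpha 0.05, target power 0.95, two-sample t-test, 42 per group. The 1:1 allocation is in section 2 (Methods). The effect is standardised, so SD = 1.

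**Formula.** With n1 and n2 patients analysed:

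- degrees of freedom: df = n1 + n2 − 2
- noncentrality: δ = d × √(n1·n2/(n1 + n2)), which is d × √(n/2) for equal groups
- power = P(|T| > t_crit), where T is noncentral t with df and δ, and t_crit is the 0.975 quantile of the central t

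**Step 1: reproduce the plan's figure.** For n = 42 per group, df = 82, t_crit = 1.989 and δ = 0.8 × √21 = 3.666. Power is 0.9518. For n = 41 per group, df = 80, t_crit = 1.990 and δ = 0.8 × √20.5 = 3.622. Power is 0.9472. So 42 is the smallest equal group size that reaches 0.95, and 84 is reproduced exactly.

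**Step 2: look for slack.** A one-sided test would need only 35 per group, so 84 is the two-sided number with nothing added for dropout. With one patient lost (42 against 41), δ = 0.8 × √(42 × 41/83) = 3.644 and power is 0.9495. With two lost (41 per group) it is 0.9472. Both still round to 0.95. With three lost (41 against 40) it is 0.9447, which rounds to 0.94.

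**Step 3: apply losses.** The documents give no attrition rate, so the rates below are assumptions. Loss is taken as equal in both arms, and the number analysed is 42 × (1 − loss), rounded down. The last column is the d for which the same formula returns 0.95.

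| Assumed loss | Analysed per group | Power at d = 0.8 | d detectable with 0.95 power |
|---|---|---|---|
| 0% | 42 | 0.952 | 0.80 |
| 10% | 37 | 0.924 | 0.85 |
| 20% | 33 | 0.893 | 0.90 |
| 30% | 29 | 0.849 | 0.96 |
| 40% | 25 | 0.792 | 1.04 |

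**Step 4: find where power falls below the usual marks.** It is 0.902 at 34 per group and 0.893 at 33, so it drops under 0.90 at a loss of about 21% (1 − 33/42). It is 0.808 at 26 per group and 0.792 at 25, so it stays at or above 0.80 up to a loss of about 38% (1 − 26/42).

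**Step 5: type II error.** At d = 0.8 it is about 5% with complete data, 11% at 20% loss (1 − 0.893) and 15% at 30% loss (1 − 0.849).

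These figures are for one comparison of two means. The calculation refers to the DERS subscales, of which Table 3 lists six, so each figure is a power per comparison.

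**The case against.** **The sample size is not miscalculated.** This stands in full. The stated inputs give 84. The fault lies in how the figure fits the sentences that follow it.

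**The decline is gradual.** This also stands. A reader might infer that 0.95 holds only if every one of the 84 patients is analysed. To the two decimals given, it survives the loss of one or two. A 10% loss costs under three points (0.952 to 0.924).

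**The powered time point may see little loss.** The end of section 1 (Introduction) ties efficacy to dysregulation before and after the intervention, which suggests T1, about two weeks after the start. Section 3.1 lets discharged patients finish in person or by teleconference. Loss at T1 could be small, with larger losses more plausible at T5. This limits how large a shortfall can be claimed, but it does not remove the problem. Section 5 does not name a time point, the Introduction also speaks of the follow-up period, and section 5 cites clinical instability as well as long follow-up as a reason for loss.

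**It is a pilot, and attrition is disclosed.** The pilot wording and the promise to report attrition soften the consequence. A reader might infer that a non-significant result will be taken as evidence against a large effect. Nothing in the document says so, and its interpretive wording points the other way. Even so, the authors chose a formal calculation at 0.95 tied to the primary objective, and the pilot label does not make that number true.

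**An analysis plan may deal with it.** A separate plan may set out how missing data are handled. It would not alter the power statement published here beside an expectation of loss.

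**Conclusion.** The point holds as a wrong statement of power. Eighty-four is the minimum with no losses (power 0.952). The same paragraph expects attrition and analyses available data only, so the power delivered will be below 0.95 once losses exceed a few patients.

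The size of the shortfall cannot be fixed from the documents. It depends on a loss rate that they do not give and on a time point that the calculation does not name. Over assumed equal losses of 10% to 40%, power at d = 0.8 runs from 0.92 down to 0.79.

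A reader might infer that the trial is underpowered. The documents do not support that: if d = 0.8 is true, power per comparison remains at least 0.80 until more than about 38% are lost. All of this assumes equal loss in both arms, and loss that leaves the true effect and SD among those analysed unchanged. Bias from loss related to outcome is a separate matter.

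**What to change.** Keep 84 randomised and change the power statement in section 5:

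1. Name the assessment time point to which the calculation applies.
2. State that 84 gives power 0.95 for d = 0.8, per DERS comparison, with complete data.
3. Add the range for assumed losses: 0.92, 0.89, 0.85 and 0.79 at 10%, 20%, 30% and 40% loss, with 0.85, 0.90, 0.96 and 1.04 as the effects detectable with 0.95 power. Label the rates as assumptions, and mark the one expected at the named time point if the sponsor has a basis for it.

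The cost is a sentence or two and a slightly less favourable stated power. No patients are added and no procedure changes.

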## Methods

2

A pilot single-centre randomized controlled intervention study was developed to be carried out at the Transition Psychiatry ward (specifically addressed to adolescents and young adults aged 15-24), Unit of Clinical Psychiatry, Department of Neurosciences/DIMSC, University Hospital of Marche Region within the Polytechnic University of Marche, Ancona, Italy. The randomization procedure will be performed using IBM Statistical Package for Social Sciences software, version 26 (SPSS, Chicago, Illinois, USA). For each participant, a random number will be generated using the RV.UNIFORM(0,1) function, which produces values distributed uniformly between 0 and 1. The cases will be then sorted according to the random number obtained and will be assigned to the two experimental groups in a 1:1 ratio. The allocation sequence will be generated by an independent researcher not involved in recruitment or intervention delivery, in order to ensure concealed allocation and minimize possible bias. The entire procedure will be documented to ensure replicability and methodological transparency.

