**Figure 1 f1:**
[figure not shown]
Timeline of the study.

At the baseline will be collected socio-demographic (e.g., sex, age, educational level, occupational and living condition) and clinical characteristics (e.g., age of onset, illness duration, number of affective and/or emotional episodes and previous hospitalizations, age at first hospitalization, comorbid physical and/or mental disorder, family psychiatry history, suicidality, drug and/or alcohol use current and/or previous, current and/or previous pharmacological and/or psychosocial and/or psychotherapy interventions) of all eligible participants through validated assessment tools. Researchers who administer assessment tools, will be blinded to patient allocation. All patients will be assessed at the following time points: a) at T0 (baseline), at least 1 day before the start of the intervention; b) at T1 (post-intervention); c) at T2 (follow-up at 1 months after completion of intervention); d) at T3 (follow-up at 3 months after completion of intervention); and, e) at T4 (follow-up at 6 months after completion of intervention); f) at T5 (follow-up at 12 months after completion of intervention). During the assessment, whereas the participant feels distressed or exhausted, the assessment will be postponed in another moment in a range of 2–3 days.

At baseline, participants will be administered the following assessment tools: Difficulties in Emotion Regulation Scale (DERS) (18), Brief Psychiatric Rating Scale (BPRS) (19), Clinical Global Impression Scale - Severity (CGI-S) (20), Coping Orientation to Problems Experienced-New Italian Version (COPE-NVI) (21), Global Assessment of Functioning (GAF) (22), Internalized Stigma of Mental Illness Inventory (ISMI) (23), Mental Health Knowledge Schedule (MAKS) (24) and the Montreal Cognitive Assessment (MoCA) (25) (**Tables 2**, **3**).

**Table 2 T2:** Timeline of the assessment administration.

Assessment	T0	T1	T2	T3	T4	T5
DERS	X	X	X	X	X	X
BPRS	X	X	X	X	X	X
CGI-S	X	X	X	X	X	X
CGI-I		X	X	X	X	X
COPE-NVI	X	X	X	X	X	X
GAF	X	X	X	X	X	X
ISMI	X	X	X	X	X	X
MASK	X	X	X	X	X	X
MOCA	X					

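### The named between-arm tests of DERS are unadjusted although every patient has a baseline DERS; they are valid, but give up precision that an ANCOVA would recover at no cost

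*Protocol article*

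**What the plan says.** All references are to the protocol article.

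- **Sample size (section 5, Statistical analysis).** The target is a "difference in the mean scores of the subscales of the DERS between the control and the experimental groups", sized "by keeping a statistical power of 0.95 to identify an effect size of 0.8 (α=0.05, two-tailed". The test behind this calculation is named only in the remark "taking into consideration all variables to be entered in the t-test". The result is: "A total sample size of 84 was established to be reached for the present study (42 participants for each group". No covariate or baseline correlation is mentioned.
- **Group comparisons (section 5).** Depending on normality, "parametric tests (t-test or ANOVA) or non-parametric tests (Kruskal-Wallis test or Mann-Whitney U test) will be used". This sentence is general and does not name DERS. The link to DERS comes from the sample-size sentence in the same section.
- **Other tests (section 5).** Longitudinal data are compared by paired t-test or Wilcoxon test. Linear and logistic regressions on patient characteristics, scale totals and subscales are planned to explore relationships between factors.
- **Data collected (section 3.2 and Table 2).** "At baseline, participants will be administered the following assessment tools: Difficulties in Emotion Regulation Scale (DERS"; Table 2 then repeats DERS at T1 to T5.
- **Objective (Introduction).** Efficacy is to be judged on emotional dysregulation before and after the intervention. How that is compared between arms is not said.
- **Limitations (Discussion).** "the diagnostic heterogeneity of participants could lead to an increased variability in outcomes".

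**The concern.** The baseline score of the outcome is often the strongest predictor of its later value. A t-test of T1 scores leaves all the variation that baseline DERS predicts in the error term. A t-test of change scores removes some of it, but adds noise when the correlation is low. The article does not say which of the two is meant.

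Three things are at stake: the width of the confidence interval for the efficacy estimate, the power left after dropout, and protection against chance imbalance. The article expects attrition, will analyse available data and does not enlarge 84 to compensate. The Methods describe simple random sorting, after which patients "will be assigned to the two experimental groups in a 1:1 ratio", with no stratification. Nothing in the design therefore balances baseline DERS, and nothing in the named tests corrects for an imbalance.

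**Working it through.** **Inputs from section 5 and the Methods.** Two-sided α = 0.05, d = 0.8, power 0.95, 42 per arm, allocation 1:1.

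**Assumed, because the documents give no figure.** Correlation r between baseline and T1 DERS of 0.3, 0.5 or 0.7, with equal variances at the two times; 34 of 42 per arm observed (8/42 = 19% loss).

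**Step 1: reproduce the stated size.** For an unadjusted two-sample t-test, power comes from the noncentral t distribution with 2n − 2 degrees of freedom and noncentrality d√(n/2).
- n = 42: 0.8 × √21 = 3.666, power 0.952.
- n = 41: power 0.947, just short of 0.95.

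So 42 per arm is the smallest size that meets 0.95. The stated 84 is exactly this test, with no covariate and no allowance for dropout.

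**Step 2: adjust for baseline.** ANCOVA multiplies the residual variance by 1 − r². The effective effect is d/√(1 − r²) with 2n − 3 degrees of freedom, and the equivalent unadjusted trial has 84/(1 − r²) patients.

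**Step 3: change scores.** The variance of a change is 2(1 − r) times that of a single score, so the effective effect is d/√(2(1 − r)).

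| | r = 0.3 | r = 0.5 | r = 0.7 |
|---|---|---|---|
| Residual variance left, 1 − r² | 0.91 | 0.75 | 0.51 |
| Fall in residual variance | 9% | 25% | 49% |
| Equivalent unadjusted N | 92 | 112 | 165 |
| Effective d, ANCOVA | 0.839 | 0.924 | 1.120 |
| Power, ANCOVA, 42 per arm (unadjusted 0.952) | 0.967 | 0.987 | 0.999 |
| Power, ANCOVA, 34 per arm (unadjusted 0.902) | 0.926 | 0.963 | 0.995 |
| Effective d, change score | 0.676 | 0.800 | 1.033 |
| Power, change score, 42 per arm | 0.865 | 0.952 | 0.997 |

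The change score cannot beat ANCOVA apart from the single degree of freedom, since 2(1 − r) − (1 − r²) = (1 − r)², which is never negative. Below r = 0.5 it is also worse than the T1-only test, because 2(1 − r) then exceeds 1.

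**Step 4: interval width.** The confidence interval shrinks by the factor √(1 − r²): 0.954, 0.866 and 0.714, or about 5%, 13% and 29% narrower.

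**Step 5: a smaller true effect.** At an assumed d = 0.5 and 42 per arm, power is 0.62 unadjusted and 0.66, 0.74 and 0.89 adjusted.

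**Step 6: chance imbalance.** The between-arm difference in mean baseline DERS has standard deviation √(2/42) = 0.218, in units of the baseline SD. A difference above 0.3 SD in either direction lies 0.3/0.218 = 1.37 standard deviations out, so it occurs in about 17% of trials of this size.

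**The case against.** The strongest reply is that nothing here is an error. In a randomised trial the unadjusted t-test is valid and unbiased, 84 is correctly computed for it, and at d = 0.8 with complete data the gain is only 1.5 to 5 points of power. The article also presents the trial as a pilot concerned with feasibility and preliminary efficacy. All of this stands, and it limits the point to efficiency. A reader might infer that the trial is undersized or its test unsound; the documents do not support that.

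A second reply is that baseline may be used after all. The objective speaks of pre- and post-intervention, so a change-score comparison is a plausible reading, and at r = 0.7 it captures most of the gain. The exploratory regressions could include both arm and baseline DERS. Both are possible, but neither is stated as the between-arm DERS analysis, and the change score loses power if r is low. The paired tests do use baseline, but within arms, so they do not estimate the randomised effect. The statistical control mentioned in the Discussion concerns concomitant treatments.

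A third reply is that covariates belong in an unseen analysis plan. That would hold if the article were silent, but it names the between-group tests and sizes the trial on one of them.

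A reader might also infer that diagnostic heterogeneity is bound to inflate variability and that adjustment would remove it. The Discussion says only that it could, and baseline DERS removes only the share of variance that it predicts.

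**Conclusion.** The point holds as an improvement in efficiency that should be made, not as the correction of a mistake. The between-arm tests that the article names ignore a baseline score that every patient provides.

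That adjustment helps at any of the correlations considered is secure. How much it helps is not, because r is assumed. Over r = 0.3 to 0.7 it is worth about 8 to 81 extra patients (92 − 84 and 165 − 84). The power gain at the design point is modest. The stronger grounds are the narrower interval, the buffer against a dropout for which 84 makes no allowance (the 19% loss used here is also an assumption), power for effects smaller than 0.8, and correction of chance baseline imbalance.

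**What to change.** State in section 5 that the between-arm efficacy analysis is an ANCOVA of post-intervention (T1) DERS on arm, with baseline DERS as covariate, reported as an adjusted mean difference with 95% confidence interval. Two things that the article leaves open must be fixed in the same place:

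- **Time point.** Name T1 as primary. The article does not designate one, so this is a choice the sponsor has to make explicitly.
- **Outcome.** Apply the model to the DERS outcome behind the sample size: each subscale adjusted for its own baseline, or the total score if that is declared primary.

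Adjust each secondary scale for its own baseline in the same way, keep the paired within-arm tests as descriptive, and keep the total at 84.

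The cost is two or three sentences. No new data or patients are needed, since Table 2 already schedules each outcome scale that is compared over time at T0. The Methods place ethics approval and recruitment in the future, so on the article's account the change can be made before any outcome is seen.
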